## Abstract

**Background:**

Primary tumor removal by cytoreductive nephrectomy in synchronous metastatic renal cell carcinoma patients has been investigated in the context of various treatment regimens. Two randomized controlled trials investigated the role and timing of cytoreductive nephrectomy in the era of targeted therapy and demonstrated that upfront nephrectomy should no longer be performed when patients require systemic therapy. Superiority of checkpoint immunotherapy agents has led to a paradigm change from targeted therapies to immunotherapy-based first-line treatment in patients with primary metastatic disease; thus, deferred cytoreductive nephrectomy needs to be verified in the immunotherapy setting. Furthermore, a need exists for personalizing treatment choices for the individual patient to avoid unnecessary overtreatment.

**Methods/design:**

To explore the impact of cytoreductive nephrectomy in this patient group receiving checkpoint immunotherapy, we initiated a randomized, controlled trial comparing deferred cytoreductive nephrectomy with no surgery. The trial integrates a comprehensive translational research program with specimen sampling for biomarker analysis.

**Discussion:**

The trial aims to show that deferred cytoreductive nephrectomy improves overall survival in patients with synchronous metastatic renal cell carcinoma, and furthermore, to identify relevant biomarkers for personalized renal cancer management.

**Trial registration:**

ClinicalTrials.gov NCT03977571 June 6, 2019.

**Supplementary Information:**

The online version contains supplementary material available at 10.1186/s12885-024-11987-3.

## Background

### Cytoreductive nephrectomy in synchronous metastatic renal cell carcinoma patients

Around 20% of patients with Renal Cell Carcinoma (RCC) have synchronous metastatic disease at diagnosis, i.e. are diagnosed with a primary kidney tumor and metastases simultaneously. Patients presenting with metastatic disease at primary diagnosis have the worst prognosis due to underlying aggressive tumor biology and are often clinically challenging due to symptoms from either the primary tumor or the metastases [1, 2]. The critical question is whether the primary kidney tumor should be removed in patients with de novo, synchronous, mRCC.

In the clinic, mRCC patients are stratified into ‘favorable’, ‘intermediate’, and ‘poor’ prognostic risk groups according to 0, 1–2, or 3–6 international metastatic renal cell carcinoma database consortium (IMDC) risk factors, respectively, with the majority (95%) of de novo synchronous mRCC patients belonging to the intermediate or poor risk group [2, 3].

Despite the improvements that targeted treatment and checkpoint immunotherapies have brought to mRCC, response rates are still overall poor across patients (reviewed in [4]). Surgical resection of the primary tumor (cytoreductive nephrectomy, CN) upon metastatic spread at diagnosis is currently recommended following systemic therapy for patients with a good general health condition, few IMDC risk factors (maximum of three), and a response to systemic therapy [5, 6]. The concept is that CN combined with systemic therapy may result in no evidence of disease and eliminate a potential source of immunosuppressive or tumor-promoting growth factors [7–9]. On the other hand, if performed initially, there is a risk for operated patients never to receive or benefit from systemic therapy due to complications following CN or rapid tumor progression, due to having their commencement of systemic treatment delayed because of surgery complications, or due to hampering of the immune response following antibiotic treatment after surgery [10]. Recently, a post hoc analysis from the JAVALIN renal 101 phase 3 trial indicated that CN may improve OS in synchronous metastatic patients receiving tyrosine kinase inhibitor and immunotherapy (TKI-IO) treatment [11].

In the era of targeted TKI therapy two randomized trials, CARMENA [12] and SURTIME [13], have questioned the role and timing of CN in synchronous mRCC patients with results pointing towards an improved benefit upon a deferred approach [13]; except for poor risk patients [7]. The deferred CN approach ensures systemic therapy for all patients, avoids systemic treatment delay, and spares surgery in patients with progressive tumors [12]. Furthermore, baseline IMDC risk features are dynamic [14, 15] and the administration of systemic therapy may change deviant blood measures and performance status of the patient, and thus change the IMDC risk score, possibly increasing surgery eligibility. However, both studies investigating the CN and TKI combinatorial effect were underpowered and performed in a previous treatment era, and thus the effect of CN in synchronous mRCC needs to be further verified in the present checkpoint immunotherapy (IO) era. Retrospective analyses have reported benefits of CN in IO-treated patients [16], however as CN only is performed in patients with a good performance status the results may be biased. To test the effect of CN in IO-treated mRCC patients the randomized prospective trial; Deferred Cytoreductive Nephrectomy in Synchronous Metastatic Renal Cell Carcinoma: The NORDIC-SUN-Trial (NCT03977571), described here, has been initiated. We aim to test the effect of deferred CN in mRCC patients receiving combination IO (IO-IO) or TKI-IO, which is currently used as standard treatment for IMDC intermediate- and poor-risk mRCC patients. Concurrently, the PROBE trial (NCT04510597) is recruiting in the US, also trying to answer this clinical question, thereby underlining its importance in the management of primary metastatic RCC.

### Predictive biomarkers for precision medicine

There is a pressing need in renal cancer patient management for reliable and clinically accessible biomarkers to predict treatment response and surgery benefit to tailor the right treatment for the individual patient hereby minimizing negative consequences to patients while assuring optimal usage of health expenses.

Immunotherapy executes its antitumor probabilities by activating the patient's own immune system. However, only little is known about the immunomodulatory and biological effects of nivolumab combined with ipilimumab, as well as the new treatment combination of TKI-IO therapy in mRCC, with the IO-IO therapy having no effect in 20% of patients with their best objective response being progressive disease [17]. Consequently, we have an urgent need for biomarkers to assure we treat the right patients. Recent studies have indicated that the treatment response may be impacted by the composition of the immune T cells as well as the microbiota (reviewed in [18]). Moreover, circulating tumor DNA (ctDNA) presents a promising sensitive tool for prognostication, detection of relapse, and monitoring of treatment response as it captures intra- and inter-tumor heterogeneity, and correlates with tumor burden [19, 20]. RCC is genetically a multistep process (loss of 3p on the one allele, followed by mutations on the other allele in *VHL*, *PBRM1*, *BAP1*, *SETD2*, and subsequently loss of 9p and 14q), with increasing tumor aggressiveness by an increasing number of genetic events [21]. Thus, mapping the genetic events may predict which patients would benefit, or not benefit, from surgery and treatment. The present trial will integrate a comprehensive translational research program with various specimen sampling for biomarker analysis using fresh frozen tumor tissue, blood samples and rectal swabs, to personalize renal cancer treatment in the future.

## Methods/design

### Rationale

The deferred CN approach enables all patients to be treated with systemic therapy, restricting only patients benefitting from the therapy to receive surgery. However, current data are derived during the TKI era and only point towards a survival benefit for CN in the subgroup patients with a maximum of 3 IMDC risk factors. In this trial we aim to describe the effect of deferred CN in a contemporary patient population treated with IO-IO or TKI-IO therapy.

Furthermore, the genomic landscape of the tumor, tumor microenvironment composition, peripheral immune subsets and the microbiome may be of great importance to the efficacy of treatment and to select candidates for surgery. To facilitate this, we will collect patient specimens longitudinally during the trial.

### Objectives and endpoints

The aim of this study is to conduct an open, randomized, multicenter comparison trial, evaluating the effect of deferred CN compared with no surgery, following initial nivolumab combined with ipilimumab or a TKI-IO-combination, in synchronous mRCC patients with ≤ 3 IMDC risk features and absence of progressive disease at metastatic sites.

### Primary endpoint

The primary endpoint is overall survival (OS) compared between synchronous mRCC patients receiving a deferred CN and patients not receiving surgery.

### Secondary endpoints include

Progression-free survival (PFS)Time to subsequent systemic therapy (TST)Objective response rate (ORR) and disease control rate (DCR) per RECIST 1.1Surgery complications and 30-day mortality (Clavien-Dindo)Fractional percentage of tumor volume to survival outcomePercentage of pathological response to survival outcomeFrequency of patients meeting the randomization criteriaOS, PFS, TST, and ORR in patients not meeting the randomization criteria and in patients with clear cell and non-clear cell histology

### Exploratory endpoints

Immune cells, tumor cells, ctDNA, and the microbiome will be analyzed and compared with OS, PFS, TST, ORR, pathological response, DCR, and safety.
Immune cells, tumor cells, ctDNA, and the microbiome will be analyzed and compared with OS, PFS, TST, ORR, pathological response, DCR, and safety.

### Study design

NORDIC-SUN is a multicenter open label randomized trial investigating the impact of CN in synchronous mRCC following 3 or 6 months of immunotherapy-based first-line treatment. Patients will be stratified by 1:1 allocation into Arm A (deferred CN) and Arm B (no surgery) based on criteria of surgical resectability, ≤ 3 IMDC risk features, and absence of progressive disease at metastatic sites. The remaining patients not eligible for randomization, referred to as Arm C, will be described, but are not a part of the main analysis.

The study design is outlined in Fig. 1.

**Fig. 1 Fig1:**
[figure not shown]
Study design. Arm **A**: Deferred CN followed by nivolumab or TKI-IO therapy. Arm **B**: No surgery, nivolumab or TKI-IO therapy. Arm **C**: Patients not eligible for randomization into Arm **A** or **B**. CN: Cytoreductive Nephrectomy; IO: Immunotherapy; mRCC: metastatic Renal Cell Carcinoma; Nivo: Nivolumab; TKI: Tyrosine Kinase Inhibitor. Generated with BioRender.com

### Study population

The trial will include 400 mRCC patients with synchronous disease. Participating centers will be University Hospitals in Denmark and the Nordic Countries, and possibly a few European sites. The coordinating center, which includes a data manager, is placed at Aarhus University Hospital, Denmark, managing the trial in close collaboration with the PI and the steering committee. Collaborating centers report to the coordinating center.

### Detailed enrollment criteria are listed below

*Inclusion criteria:*
Synchronous mRCC proven with a core needle biopsy (all histological subtypes are acceptable) and measurable as per RECIST v 1.1.Age > 18.Patients referred to standard immunotherapy-based first-line treatment according to the recommendations by the European Medicines Agency and the national health authorities. Both IO-IO and TKI-IO are considered as a standard treatment.Females not pregnant. Fertile patients must use effective means of contraception.Life expectancy > 4 months.Karnofsky Performance status > 70.Laboratory values acceptable for IO-IO or TKI-IO treatment.Able to speak and understand native language.
*Exclusion criteria:  *
Prior systemic treatment for mRCC.Other cancer diagnosis within three years (except in situ basal cell carcinoma and radically treated localized prostate cancer with undetectable prostate-specific antigen).Major surgical procedure, open surgical biopsy, or significant traumatic injury within 14 days prior to enrollment, or non-healed lesion.Clinically significant (i.e. active) cardiovascular disease for example cerebrovascular accidents (< 6 months before inclusion), myocardial infarction (< 6 months before inclusion), unstable angina, New York Heart Association grade II or greater congestive heart failure.No symptomatic brain metastasis requiring systemic corticosteroids (> 10 mg daily prednisone equivalent).Recent (within the 30 days prior to inclusion) treatment with another investigational drug.Any active or recent history of a known or suspected autoimmune disease or recent history of a condition that requires systemic corticosteroids (> 10 mg daily prednisone equivalent) or other immunosuppressive medications, excluding inhaled steroids and local cutaneous steroids. Subjects with vitiligo or type I diabetes mellitus or residual hypothyroidism due to autoimmune thyroiditis only requiring hormone replacement, psoriasis not requiring systemic treatment are permitted to enroll.Known hypersensitivity to monoclonal antibodies.Known history of testing positive for human immunodeficiency virus or known acquired immunodeficiency syndrome (AIDS).Any positive test for hepatitis B- or C-Virus, indicating acute or chronic infection.

### Randomization and masking

Patients are randomized 1:1 into the two treatment arms:ARM A: 3 months of IO-IO or TKI-IO followed by deferred CN, followed by maintenance nivolumab or a TKI-IO-combination.ARM B: No surgery, 3 months of IO-IO or TKI-IO followed by maintenance nivolumab or a TKI-IO-combination.

Patient eligible for surgery is randomized by a local project nurse using a computer-generated allocation sequence and is not blinded due to the circumstances; surgery versus no surgery. In Arm A patients are treated according to standard protocol with first-line IO-IO or TKI-IO combination treatment followed by a CN. In Arm B patients are receiving standard IO-IO or a TKI-IO combination first-line treatment (Fig. 1). Patients will be stratified by treatment choice (IO-IO vs TKI-IO).

The remaining patients, referred to as Arm C, not eligible for randomization due to > 3 IMDC risk factors, progressive disease at metastatic sites, poor performance or a non resectable tumor will undergo three months of nivolumab or a TKI-IO combination and then be evaluated again after another 3 months. If still not eligible for randomization, the patients will continue nivolumab maintenance and TKI-IO combination and be followed on survival.

### Study procedure

Patients included in the NORDIC-SUN trial are stratified according to institution, treatment choice, number of IMDC risk factors, and combined elevated neutrophil–lymphocyte ratio and hyponatremia.

All patients will receive systemic IO-IO or TKI-IO immediately after inclusion. After three months of nivolumab combined with ipilimumab or a TKI-IO combination, the patient will be discussed for resectability at the multidisciplinary meeting (MDT), whether the patient is eligible for CN. Patients with ≤ 3 IMDC risk factors and deemed suitable for CN including an acceptable performance status and absence of progression at metastatic sites will then undergo randomization. Patients deemed not suitable for surgery or have > 3 IMDC risk features at the 3 month evaluation continue systemic therapy for 3 months, followed by a 2nd evaluation 6 months after inclusion. Patients with ≤ 3 IMDC risk factors and deemed suitable for CN at 2nd evaluation will then undergo randomization. Patients deemed not suitable for surgery or have > 3 IMDC risk features at the 6 month evaluation continue systemic therapy (Arm C). Nivolumab may continue until unacceptable toxicity or total treatment length of two years from inclusion. Allocating patients to Arm C promotes participant retention, securing outcome data of patients not randomized.

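### Whether a patient is randomised at 3 or 6 months is in neither stratification list nor the stated adjustment; add it to the primary survival analysis

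*Protocol article*

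**What the plan says.** Study design describes surgery "following 3 or 6 months of immunotherapy-based first-line treatment", so there are two routes to randomisation. Study procedure gives the sequence:

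- Treatment comes first: "All patients will receive systemic IO-IO or TKI-IO immediately after inclusion".
- At 3 months, patients with at most three IMDC factors who are "suitable for CN including an acceptable performance status and absence of progression at metastatic sites will then undergo randomization".
- Those not suitable, or with more than three factors, continue therapy and are evaluated again at 6 months. Those with at most three factors and "deemed suitable for CN at 2nd evaluation will then undergo randomization".

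The stratification factors appear twice. Study procedure says "Patients included in the NORDIC-SUN trial are stratified according to institution, treatment choice, number of IMDC risk factors", and adds a fourth factor that combines a raised NLR with low sodium. Randomization and masking names one factor only: "Patients will be stratified by treatment choice (IO-IO vs TKI-IO". Data analysis plans a two-sided log-rank test, and Kaplan–Meier and Cox analyses with and without adjustment for the stratification factor, in the singular. None of the three mentions evaluation time.

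Two further statements bear on this. The Background says that "baseline IMDC risk features are dynamic", and the Discussion expects first-line therapy to lower the score in some patients and so make more of them eligible. The arm definitions under Randomization and masking mention only 3 months of therapy before surgery or continued treatment.

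**The concern.** Patients randomised at 6 months are selected differently from those randomised at 3 months. They were judged ineligible at the first evaluation (too many IMDC factors, progression at metastatic sites, poor performance or an unresectable tumour) and have had three more months of therapy when the comparison starts. Their prognosis may well differ. The variable is known for every patient before allocation, yet no stated factor or adjustment uses it. If it is prognostic, chance imbalance between arms stays in the primary comparison, and an analysis that ignores it is less powerful than one that uses it.

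A related gap is that two of the listed factors, the IMDC count and the NLR/sodium status, have no stated time of measurement. The article itself says that the IMDC count changes on therapy. A patient included with more than three factors and randomised with three or fewer necessarily has different counts at the two times, so sites could enter different values for the same factor.

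**Working it through.** **1. The plan's own figures.** From Sample size determination: 400 × 0.60 = 240 randomised, 120 per arm; 168 deaths; 80% power; 5% level; 50% improvement in overall survival, read here as HR = 1/1.5 = 0.667 (the HR is not stated).

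- Schoenfeld, two-sided: deaths = 4 × (1.960 + 0.842)² / (ln 1.5)² ≈ 191.
- Power at 168 deaths: Φ(√168/2 × ln 1.5 − 1.960) = Φ(0.668) ≈ 74.8%.

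The 168 is therefore not reproduced by this formula. The plan used simulation with inputs it does not show. That is a separate matter; 168 deaths serves here only as the setting.

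**2. Where evaluation time appears.**

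| Section | Content | Evaluation time included? |
|---|---|---|
| Study design; Study procedure | randomisation at 3 or 6 months | yes, as two entry points |
| Randomization and masking, arm definitions | 3 months only | no |
| Randomization and masking, stratification | treatment choice | no |
| Study procedure, stratification | institution, treatment choice, IMDC count, NLR/sodium | no |
| Data analysis | adjusted and unadjusted for the stratification factor | no |

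**3. Chance imbalance.** With 120 per arm and late-route share p, the 95% range of the between-arm difference is ±1.96 × √(2p(1 − p)/120):

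- p = 0.10: ±7.6 points
- p = 0.20: ±10.1 points
- p = 0.40: ±12.4 points

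**4. Power and type I error.** Simulation of 4,000 trials per setting, 120 per arm. Assumptions not in the article: exponential survival, control median 24 months, 36–72 months of follow-up, and the late-route share and route HR shown. The tests are an unstratified log-rank and a log-rank stratified by route.

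| Late share | Route HR | Power, unstratified | Power, stratified | Gain (points) |
|---|---|---|---|---|
| 20% | 1.5 | 75.5% | 76.8% | 1.3 |
| 20% | 2.0 | 74.3% | 76.6% | 2.3 |
| 40% | 1.5 | 77.1% | 77.7% | 0.6 |
| 40% | 2.0 | 74.4% | 78.9% | 4.5 |

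These runs averaged about 176 to 189 deaths. Simulating at 168 deaths instead, over the same shares and route HRs, gives a gain of about 0 to 5 points. If route is not prognostic at all, stratifying by it costs at most about 0.5 point. With no treatment effect, rejection rates were 4.9–5.4% unstratified and 4.6–5.4% stratified.

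**5. Room in the randomisation.** Assuming 10 institutions and two levels for each of the other three listed factors, there are 10 × 2 × 2 × 2 = 80 cells for 240 patients, or 3 per cell. A further two-level factor would make 160 cells, or 1.5 per cell.

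**The case against.** The strongest reply is that nothing here is an error. Both arms are allocated at the same point within each route, so the comparison is valid with or without adjustment. The article is a condensed account, and covariate choice is ordinary content for an analysis plan that is not shown. Four listed factors already make thin cells, so omitting a fifth from the randomisation is defensible. Much of this stands: there is no bias and no alpha inflation, and the absence is established only for this article. But the article does state its factors and its adjustment, and the two-route design makes evaluation time an obvious candidate that those statements omit.

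Three stronger readings are tempting and not supported:

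- A reader might infer that stratification is carried out at inclusion, on outdated values. The sentence gives no time point; patients included in the trial may simply mean participants, and the other list sits under randomisation. Values at inclusion would in any case be valid pre-randomisation covariates.
- A reader might infer a larger power gain. Stratifying on route (20%, HR 2.0) together with an IMDC grouping (30%, HR 2.0) moves simulated power from 67.0% to 72.4%, but the IMDC count is already a listed factor, so that gain is not due to route alone.
- In the same simulation the mean HR is 0.689 unstratified and 0.666 stratified. That is the usual gap between marginal and conditional HRs, and the article does not say which its target effect is.

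**Conclusion.** The point holds as a missed improvement in precision, not as a flaw in validity. Evaluation time separates patients who qualified at once from those who first failed the criteria, and it appears in no stated factor or adjustment. Using it would be worth roughly 0 to 5 points of power at 168 deaths and HR 0.667. That rests on an assumed 20–40% late share and a route HR of 1.5–2.0; the article gives neither, and offers no data on whether late entrants do worse once they meet the criteria. The possible loss if they do not is about half a point at most. The undefined measurement time of the IMDC and NLR/sodium factors, and the arm definitions limited to 3 months, are wording defects at the same place.

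**What to change.** 1. Prespecify evaluation time (3 versus 6 months) as a stratum in the primary log-rank test of overall survival, or as a covariate or stratum in the Cox model. Do not add it to the randomisation cells, and do not drop institution to make room for it.
2. State that the IMDC count and NLR/sodium status used as factors are those at the evaluation leading to randomisation.
3. Reconcile the arm definitions under Randomization and masking with the two entry points in Study design and Study procedure.

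The cost is small. Evaluation time and IMDC count are known at randomisation because they determine eligibility. NLR and sodium are not stated eligibility criteria, so their availability at that visit should be confirmed; Sample collection schedules blood at weeks 12 and 24 but does not name these measures. Existing allocations stand, and the adjustment applies to all randomised patients. The article reports 40 of 400 patients included, so the change can be made well before any outcome analysis.
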